### **8.3. STUDY SETTINGS**

The study will be conducted in approximately 4 hospitals in western Kenya and at least 3 in Uganda, each located in areas with moderate to intense malaria transmission. Below is a list of suggested first choice and back-up hospitals where the study will be conducted. The list is not exhaustive and

subject to change following exploration and review of the above mentioned eligibility criteria and participant recruitment rates.

### 8.3.1. Kenya

Approximately eight hospitals in western Kenya will be chosen from a list of Government or private (e.g. mission) hospitals in the previous Western and Nyanza Provinces, based on patient numbers, available infrastructure and malaria transmission and planned malaria control interventions in the catchment area.

#### 8.3.1.1. Suggested primary hospitals and neighbouring satellite clinics

1. *Siaya County Referral Hospital*: Siaya Town, Siaya County, western Kenya. The 240-bed hospital is located in an area of high perennial malaria transmission in the lake region and serves mainly a rural population. This is the main public hospital in the district, with a total of 260 beds, including 60 beds in the paediatric unit.
2. *Kisumu County Referral Hospital*: 195-bed government facility located in Kisumu county, in Kisumu town, in an area of moderate
3. *Jaramogi Oginga Odinga Teaching and Referral Hospital*: Government owned 467 bed capacity hospital located in Kisumu County in Kisumu town in an area of moderate transmission of malaria.
4. *Migori County Referral Hospital*: Is a 180 bed capacity hospital 3 hours away from Kisumu located in Migori county in Migori town, South western part of Kenya in an area with moderate –high transmission of malaria
5. *Ahero County Hospital*: A 50 bed government facility located in Ahero town, Kisumu County, western Kenya, located 20 Km, approximately 30 min drive from Kisumu.
6. *Rabuor sub County Hospital*: A 30 bed government facility located in Rabuor township, Kisumu County, western Kenya, located 10 Km, approximately 15 min drive from Kisumu.
7. *Kombewa County Hospital*: A 90 bed government facility located in Kombewa township, Kisumu County, western Kenya, located 30 Km, approximately 40 min drive from Kisumu.
8. *Pastor Machage Memorial Hospital, Migori*: A 115 bed Private facility located in Migori town, Migori County (formerly South Nyanza). The facility is ~200Km (3-hour drive from Kisumu)

#### 8.3.1.2. Backup Hospitals and neighbouring satellite clinics

9. *Homa Bay District Hospital*: This is a 280 bed government facility in Homa Bay County, appr. 2 hours drive (110km) from Kisumu, in an area of intense malaria transmission
10. *St Mary's Hospital, Mumias*: This is a 200 bed mission hospital located in Mumias town, 1.5 hours drive from Kisumu, in an area with moderate malaria transmission
11. *Mukumu Mission Hospital*: This is a 228-bed mission hospital located on the road between Kisumu and Kakamega town in an area with moderate malaria transmission
12. *Kisumu District Hospital*: 195-bed government facility located in Kisumu town, in an area of moderate malaria transmission.
13. *Busia District Hospital*: 185-bed government facility, located in Busia town at the Kenyan-Ugandan border, Busia County, Western Province. Distance to Kisumu 110km, appr. 2 hours drive. Intense malaria transmission.
14. *Nyamira District Hospital*: 203-bed government facility, located in Nyamira County, 1.5 hours drive from Kisumu.

15. *Rachounyo sub county hospital*: Government owned 80 bed capacity hospital located in Homabay County, in Oyugis town, in an area of moderate malaria transmission. Distance ~80 KM (1 hour drive from Kisumu)
16. *Bondo District Hospital*: This 50-bed hospital is located in Bondo town, Siaya County, western Kenya, located 50 kilometres west of Kisumu in an area with intense malaria transmission.
17. *St. Joseph's Mission Hospital-Ombo*: A 150 bed Private facility, owned by the Catholic diocese of Homa Bay, located in Migori town, Migori County (formerly South Nyanza). The facility is ~200Km (3-hour drive from Kisumu)
18. *Nyakach sub County Hospital*: A 40 bed government facility located in Pap Onditi township, Kisumu County, western Kenya, located 35 Km, approximately 45 min drive from Kisumu.

### 8.3.2. Uganda

#### 8.3.2.1. Primary hospitals and neighbouring satellite clinics

1. *Tororo general Hospital*: A 200-bed public hospital located in Tororo district in the eastern part of Uganda, and area with intense perennial malaria transmission.
2. *Hoima Regional Referral hospital*: A Government owned regional referral hospital located in the mid-western part of the country serving an area of intense malaria transmission.
3. *Jinja Regional Referral Hospital*: A regional referral hospital located in the central region serving an area along the shores of Lake Victoria with moderate and seasonal malaria transmission.
4. *Masaka Regional Referral Hospital*: A 350-bed hospital located in the south-western part of the country. It serves the people living along the shores of Lake Victoria; this is an area of seasonal malaria transmission.

#### 8.3.2.2. Backup hospitals and neighbouring satellite clinics

5. *Lira Regional Referral Hospital*: A 350-bed referral hospital in the northern part of Uganda serving 8 districts in the Lango sub-region including the Apac district. This is an area with intense malaria transmission. Recruitment will be expanded to this hospital if recruitment in the other hospitals is slower than anticipated.
6. *Soroti Regional Referral Hospital*: Soroti Hospital is a 200+ bed hospital in the town of Soroti, in Soroti District, in eastern Uganda.
7. *Gulu Regional Referral Hospital*: Gulu Hospital is a 250-bed hospital in Gulu town, northern Uganda.
8. *Mubende Regional Referral Hospital*: A regional referral hospital located in the central region, an area with moderate and seasonal malaria transmission
9. *Arua Regional Referral Hospital*: A regional referral hospital located in West-line sub-region, an area with high to moderate malaria transmission
10. *Iganga general Hospital*: A 200-bed public hospital located in Iganga district in the eastern part of Uganda, along the shores of Lake Victoria an area with high to moderate malaria transmission.
11. *Kamuli Mission Hospital*: A 200-bed catholic- mission hospital located in Kamuli district in the eastern part of Uganda, along the shores of Lake Kyoga an area with moderate malaria transmission.

## 8.4. ELIGIBILITY CRITERIA

For a description of the pre-study screening procedures see section 8.7.2, 'Visit 1: Pre-screening', page 37.

### 8.4.1. Eligibility criteria for Pre-Study Screening

#### 8.4.1.1. Inclusion criteria for enrolment into pre-study screening period

1. Haemoglobin <5.0 g/dl or PCV < 15%, or requirement for blood transfusion for other clinical reasons on or during admission to the hospital
2. Aged less than 59.5 months
3. Body weight ≥5 kg
4. Resident in catchment area

#### 8.4.1.2. Exclusion criteria for enrolment into pre-study screening period

1. Recognised specific other cause of severe anaemia (e.g. trauma, haematological malignancy, known bleeding disorder)
  2. Known sickle cell disease
  3. Anticipated to reach the 5th birthday (60 months of age) within 2 weeks from enrolment (i.e. prior to randomization)
  4. Child will reside for more than 25% of the 6 months study period (i.e. 6 weeks or more) outside of catchment area
- Hereditary polymorphisms, other than sickle cell disease, that are known to provide protection against severe forms of malaria but may also cause severe anaemia, including thalassaemias and G6PD deficiency are not exclusion criteria as no specific malaria control policies are recommended for these groups (by contrast to sickle cell disease).
  - HIV infection and cotrimoxazole prophylaxis are not exclusion criteria.

### 8.4.2. Eligibility criteria for enrolment into study

For a description of the study procedures criteria see section 8.7.3 , 'Visit 2: Screening interview and consent', page 38.

#### 8.4.2.1. Inclusion criteria for enrolment:

1. Fulfilled the pre-study screening eligibility criteria
2. Aged < 59.5 months
3. Clinically stable, able to take oral medication
4. Subject completed blood transfusion(s) or became clinically stable without transfusion
5. Able to feed (for breastfeeding children) or eat (for older children)
6. Absence of known cardiac problems
7. Provision of informed consent by parent or guardian

#### 8.4.2.2. Exclusion criteria for enrolment:

10. Previous enrolment in the present study
11. Known hypersensitivity to study drug
12. Sickle cell disease

13. Use or known need at the time of enrolment for concomitant prohibited medication (see section 8.5.7.2, page 35) during the 14 weeks PMC treatment period (see section 8.5.7.2, page 35).
14. Ongoing or planned participation in another clinical trial involving ongoing or scheduled treatment with prohibited medicinal products or active follow-up during the course of the study (6 months from enrolment)
15. A known need at the time of enrolment for scheduled surgery during the subsequent course of the study (6 months from enrolment)
16. Suspected non-compliance with the follow-up schedule
17. Known heart conditions, or family history of congenital prolongation of the QTc interval.
18. Taking medicinal products that are known to prolong the QTc interval

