##### *Prohibited medication*

- Antimalarials not prescribed by the study: Chloroquine, halofantrine, mefloquine
- Diuretics (hydrochlorothiazide, furosemide)
- Drugs known to prolong the QT interval
  - Antimicrobials:
    - macrolides (e.g. erythromycin, clarithromycin, azithromycin, roxithromycin),
    - fluoroquinolones (e.g. ciprofloxacin, norfloxacin, levofloxacin, moxifloxacin, sparfloxacin)
    - pentamidine
  - Antifungals: ketoconazole, fluconazole, itraconazole, posaconazole, voriconazole, caspofungin
  - Antiretrovirals: ARVs, specifically: indinavir, nelfinavir, atazanavir, saquinavir
  - Antiarrhythmic agents (e.g. amiodarone, sotalol)
  - Non-sedating antihistamines (astemizole, terfenadine)
  - Antipsychotics (neuroleptics): Haloperidol, Thioridazine
  - Antidepressants: Imipramine, Citalopram, Escitalopram
  - Antiemetics: Domperidone, Chlorpromazine, Ondansetron

Randomised participants who take prohibited medications resulting in the premature cessation of the study intervention, will remain in the trial and will be included in the primary, intention-to-treat analysis, but excluded from the per-protocol analysis.

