PQ is currently only available in the fixed dose combination with dihydro-artemisinin (DHA) as DP. The DHA component, eliminated within a few hours, is not expected to provide a significant contribution to the effect of IPTp, yet may provide a degree of protection against the development of PQ resistance in the parasite population. DP is registered in both Kenya and Uganda, initially as Duo-Cotecxin®, manufactured by Beijing HolleyCotec, and recommended by the Kenyan Ministry of Health as second-line treatment since 2009, and approved in March 2012 by the Ugandan National Drug Authority (NDA) for treatment of malaria and to comply with the Current Good Manufacturing Practice (cGMP) regulations enforced by the Uganda authorities.

Piperaquine is well tolerated. Side effects in adults include transient drops in haemoglobin by day 7 (seen with all artemisinins), headache, weakness and fever. The main safety concerns with piperaquine relate to its dose-dependent QTc prolongation. Transient QTc prolongation has been confirmed in clinical trials, but these were mild and similar to many other anti-malarials and there is no indication from clinical data signalling that it is associated with clinically significant arrhythmias. This is consistent with recent in-vitro models which confirmed that despite mild QTc prolongation, the potential cardiac proarrhythmic risk with piperaquine is low and similar to that observed with lumefantrine (the long-acting component in Coartem), and lower than for chloroquine. This study concluded that DP does not appear to induce potential torsadogenic effects in vitro (which could result in life threatening abnormality of heart rhythm).

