#### 2. BEFORE YOU OR YOUR CHILD TAKE EURARTESIM

**Do not take Eurartesim if you or your child:**

- is allergic (hypersensitive) to the active substances, piperaquine tetraphosphate or dihydroartemisinin, or to any of the other ingredients of Eurartesim (see section 6 for a list of these);
- has a severe type of malaria infection which has affected parts of your body such as the brain, lungs or kidneys;
- has a heart condition, such as changes to the rhythm or rate of your heart beat, or heart disease;
- knows that any member of your family (parents, grandparents, brothers or sisters) died suddenly due to a heart problem or was born with heart problems;
- suffers from changes to the levels of salts in your body (electrolyte imbalances);
- is taking other medicines that can have an effect on heart rhythm, such as:
  - quinidine, disopyramide, procainamide, amiodarone, dofetilide, ibutilide, hydroquinidine or sotalol;
  - medicines used to treat depression;
  - medicines used to treat mental health problems such as phenothiazines, sertindole, sultopride, chlorpromazine, haloperidol, mesoridazine, pimozide, or thioridazine;

- medicines used to treat infections. These include some of the types of medicines used to treat bacterial infections (macrolides [such as erythromycin or clarithromycin] and fluoroquinolones [such as moxifloxacin and sparflaxacin]) or fungal infections (including fluconazole and imidazole) as well as pentamidine (used to treat a specific type of pneumonia) and saquinavir (for treatment of HIV);
- antihistamines used to treat allergies or inflammation such as terfenadine, astemizole or mizolastine;
- certain medicines used to treat stomach problems such as cisapride, domperidone or droperidol;
- other medicines such as vinca alkaloids and arsenic trioxide (used to treat certain cancers), bepridil (used to treat angina), diphemanil (used to treat stomach disturbances), levomethadyl and methadone (used to treat drug addiction), and probucol (used to treat high blood cholesterol levels).
- has recently (for example within about one month) been treated for malaria with certain medicines or has taken certain medicines to prevent malaria. These medicines include: mefloquine, halofantrine, lumefantrine, chloroquine or quinine

If any of the above applies to you or your child or if you are unsure, tell your doctor or pharmacist before taking or giving Eurartesim.

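### The family-history part of enrolment exclusion 17 is narrower than the appended Eurartesim leaflet: sudden cardiac death and heart defects in close relatives are not covered, and no reason is given

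*Protocol*

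**What the plan says.** Three criteria in section 8.4.2 deal with cardiac or QT risk at enrolment:

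- Inclusion 6 requires "Absence of known cardiac problems". It concerns the child only.
- Exclusion 17 reads "Known heart conditions, or family history of congenital prolongation of the QTc interval". Section 3.1 repeats it as enrolment exclusion 8. The narrative summary (section 3.2) mentions heart conditions but no family history.
- Exclusion 18 reads "Taking medicinal products that are known to prolong the QTc interval". It is backed by the prohibited list in section 8.5.7.2, which also names diuretics.

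The leaflet in section 16.8 lists reasons not to take the drug. One is that the patient or caretaker "knows that any member of your family (parents, grandparents, brothers or sisters) died suddenly due to a heart problem or was born with heart problems". Another is that the patient "suffers from changes to the levels of salts in your body (electrolyte imbalances".

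On the risk itself, section 11.8.1.2 says: "The main safety concerns with piperaquine relate to its dose-dependent QTc prolongation".

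**The concern.** The protocol appends a product leaflet and then sets a family-history criterion narrower than the one in that leaflet. The two also differ in kind: exclusion 17 names one diagnosis in relatives, while the leaflet names an event (sudden death from a heart problem) and a wider class of conditions (being born with heart problems). A site following section 8.4.2.2 to the letter would enrol a child whose sibling died suddenly of a heart problem, provided that no diagnosis of congenital QTc prolongation had been made in the family. The leaflet says such a child should not take the drug.

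The gap falls on the protocol's own main named safety concern. An ECG could act as a second check at entry, but section 9.6.1 plans ECGs only in the cardiac sub-study. The rule there that excludes a confirmed baseline QTc of 450 ms or more can therefore operate only on those children.

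**Working it through.** The main check is a comparison of passages. The only arithmetic concerns the size of the ECG sub-study.

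**Leaflet items against the eligibility criteria (sections 8.4.1 to 8.4.3, and the copies in 3.1 and 3.2)**

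| Leaflet item (section 16.8) | Covered by a criterion? |
|---|---|
| Heart condition in the child | Yes: inclusion 6 and exclusion 17 |
| Medicines affecting heart rhythm | Addressed: exclusions 13 and 18 and section 8.5.7.2; prohibited medication is checked again at randomisation |
| Close relative born with heart problems | Only in part: congenital QTc prolongation is one such problem; others are not covered |
| Close relative who died suddenly of a heart problem | No, unless congenital QTc prolongation is also known in the family |
| Electrolyte imbalance | No; the nearest provision is the ban on diuretics |

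The pre-screening criteria in 8.4.1 contain no cardiac item. The randomisation criteria in 8.4.3 add clinical stability and a second check on prohibited drugs, but no family history.

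**Is the narrower wording explained?** The protocol argues several of its other departures from the leaflet. Section 8.5.2.4 bases dosing on WHO guidelines. Section 8.5.2.5 discusses the manufacturer's food advice and answers it from study experience. Sections 8.5.2.5 and 11.8.1.2 support repeated monthly courses with a review, ECG data and trial results. Nothing comparable is said about family cardiac history.

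**Who has an ECG?** Section 8.8.2 gives 26 evaluable children (difference 20 ms, SD 31, power 90%, two-sided alpha 0.05), 33 per arm after 20% loss, and 66 in total. A paired normal approximation reproduces this:

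- n = ((1.960 + 1.282) × 31/20)² = 25.2, rounded up to 26
- 26/(1 − 0.20) = 32.5, rounded up to 33
- 33 × 2 = 66

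Against the current target of 1040, 66/1040 = 6.3% have a planned ECG. The other 1040 − 66 = 974 (93.7%) have none. This describes how much ECG screening backs up the history. It does not measure how many children the wording affects.

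**Exposure of one such child.** Three courses of three daily doses is 3 × 3 = 9 doses if allocated to DP.

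**The case against.** **The leaflet is not the protocol's standard.** It is a user leaflet for treating uncomplicated malaria, and no section says that eligibility follows it. The trial departs from it more broadly, in dosing bands, food advice, number and spacing of courses, and use of DP about two weeks after lumefantrine. The safety-reporting flowchart also refers to an Investigator's Brochure that is not at hand. This stands as far as it goes: a sponsor may depart from a leaflet. It does not remove the point, because a stated reason is what is missing here.

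**Other safeguards exist.** The child's own cardiac history, QT-prolonging drugs and diuretics are all screened or restricted. Section 8.5.4 allows removal from therapy for safety. The cardiac sub-study runs at the start of the trial with DMEC review, and the TSC may add QTc screening for the remaining children. All of this is true and lowers the risk. It would be wrong to call exclusion 17 the only QT screen, or to suggest that QT risk is neglected. But none of these safeguards asks about the family histories at issue.

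**The electrolyte item is weaker.** It is neither family nor cardiac history. Section 8.7.3.5 does not name electrolytes among the baseline tests, and other results are recorded only where they happen to have been done. The first DP dose comes about two weeks after enrolment, following a second check of clinical stability, so an imbalance seen during admission may have resolved. This stands, and the item is kept only as a secondary point.

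**Stronger readings a reader might infer.** One is that 94% of children are affected because they have no ECG. That does not follow: the 66 ECG children face the same exclusion 17, and an ECG in the child does not reveal a relative's sudden death. Another is that the number enrolled against the leaflet can be estimated. The documents give no prevalence for these histories, so any count would rest wholly on an assumed rate. A third is that the criteria were never checked against the leaflet when it was added. The version 2 entry in the amendment log lists no eligibility change, but that does not show that no check was made.

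**Conclusion.** The point holds in a limited form. Exclusion 17 and its copy in section 3.1 restrict family cardiac history to congenital QTc prolongation. The appended leaflet is wider on two items, sudden cardiac death and heart defects in close relatives. No criterion covers the first, and the second is covered only through congenital QTc prolongation. The protocol gives no reason for the difference.

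The number of children concerned is unknown and may well be small. The conclusion does not depend on it. It rests on two things visible in the protocol: the two texts disagree, and the disagreement concerns the risk that the protocol itself puts first. Power and the primary analysis are not in question. The matter is worth correcting because, followed as written, the criteria admit children whom the appended product information says should not take the drug. Which rule is clinically right is not judged here.

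**What to change.** Reconcile exclusion 17 in section 8.4.2.2, and item 8 in section 3.1, with the leaflet in section 16.8 on family history. Either bring the wording into line or state why the narrower criterion is used. The clinical team should make that choice.

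The cost is at most one reworded criterion in two places and one caretaker question at enrolment. If the criterion is widened, a few children may become ineligible. A change would apply only to children not yet enrolled.

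As a secondary step, the clinical team should also reconcile the leaflet's electrolyte item with the eligibility criteria, bearing in mind that section 8.7.3.5 does not name electrolytes among the baseline tests and that first dosing follows enrolment by about two weeks.

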### 8.4.3. Eligibility criteria for randomisation into study (at 2 weeks)

#### 8.4.3.1. Inclusion criteria for randomisation:

1. Fulfilled enrolment eligibility criteria and was enrolled during recent admission
2. Aged <60 months
3. Still clinically stable, able to take oral medication, able to feed (for breastfeeding children) or eat (for older children) and able to sit unaided (for older children who were already able to do so prior to hospitalisation)

#### 8.4.3.2. Exclusion criteria for randomisation:

1. Used DP since enrolment
  2. Use or known need at the time of randomisation for concomitant prohibited medication (see section 8.5.7.2, page 35) during the 14 weeks PMC treatment period (see section 8.5.7.2, page 35).
  3. Enrolled, or known agreement to enrol into another clinical trial involving ongoing or scheduled treatment with medicinal products during the course of the study (6 months from enrolment)
  4. A known need at the time of randomisation for scheduled surgery during the subsequent course of the study (6 months from enrolment)
  5. Suspected non-compliance with the follow-up schedule
  6. Withdrawal of consent since enrolment
- Readmission or re-transfusion in the 2 week period since enrolment or on the day of randomisation screening is not an exclusion criteria for randomization but require a delay of randomisation so that a minimum of 12 days and a maximum of 21 days have passed since the most recent discharge if artemether-lumefantrine was provided around the time of (re)discharge, provided the patient has clinically recovered and is stable and fulfils the randomisation eligibility criteria on the re-scheduled day of randomisation.

---

 See Section 8.5.7.2 “Concomitant and prohibited Medications”, page 34

- Fever ( $\geq 37.5^{\circ}\text{C}$ ) on the day of randomisation screening is not an exclusion criteria for randomization but requires a delay of randomisation. Febrile children will be screened for malaria using RDTs or malaria smears, and RDT or smear positive children will be treated with a repeat course artemether-lumefantrine. They will be eligible for randomisation when a minimum of 12 days and a maximum of 21 days have passed since the first day of the repeat course of artemether-lumefantrine, provided the patient has clinically recovered and is stable and fulfils the randomisation eligibility criteria on the re-scheduled day of randomisation.

